### Sample

The R software was used to determine the sample size. Linear mixed model analysis was used to perform the calculation (package sjstats version 0.18.1), power = 80%; *α* = 0.05; large effect size of 1.25; number of clusters = six (three groups × two conditions). Using these parameters, the minimum sample size is 26 participants, to which 10% will be added to compensate for possible dropouts, leading to a sample of 29 participants.

The inclusion criterion is a clinical diagnosis of PFOA [30] adapted from the National Institute for Health and Care Excellence (NICE) guidelines [31]. The following criteria will also be required for inclusion: (i) age 50 years or over; (ii) anterior or retropatellar knee pain aggravated by at least two activities that place strain on the patellofemoral joint (e.g. squatting and stair ambulation); (iii) pain during these activities on most days in the previous month; (iv) pain severity during aggravating activities of ≥ 3 on an 11-point numerical rating scale; (v) symptoms present for at least three months; and (vi) no morning joint stiffness lasting longer than 30 min. The participants will need to have the ability to perform a single-leg squat to at least 60° of knee flexion and have a body mass index between 25 and 34.9 kg/m^2^.

The exclusion criteria are as follows: (i) recent treatment (e.g. knee injections within the previous 3 months); (ii) history of hip, knee, or foot surgery; (iii) physical inability to undergo the testing procedures; (iv) concomitant pain in other knee structures (including the tibiofemoral joint), hip, or lumbar spine; (v) history of knee or hip arthroplasty/osteotomy; (vi) neurological or systemic arthritis; (vii) use of a cane or other gait-assistance device; (viii) history of patellar fracture or recurrent subluxation; and (ix) score on the Mini Mental State Examination (MMSE) suggestive of dementia, taking into account the participant’s educational level.

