**Fig. 1 Fig1:**
[figure not shown]
Study design

The assessment will be performed on the affected lower limb in cases of unilateral PFOA or on the more painful knee in cases of bilateral PFOA [24]. If the participant reports equal pain intensity in both lower limbs, the lower limb to be tested will be chosen randomly using a simple raffle. For all evaluations, the participants will wear shorts, sports tops (in the case of women), and the same type of shoes (Nike® model *Flex Experience RN 2 MSL*), which will be provided to them by the assessors. The primary and secondary outcomes will be investigated during the performance of two functional tasks: level-ground walking and single-leg squat test.

Data collection and the therapeutic implementation steps will be performed by different assessors during the entire course of the study. Prior to data collection, the participants will have a period of familiarisation with both functional tasks and both therapeutic approaches that will be applied. The participants will perform the two functional tasks in a standardised order. The first will be level-ground walking at a self-selected pace and second will be the single-leg squat test, which is associated with a progressively larger patellofemoral joint load.

The presence of any pain or disability that may be related to the interventions and/or functional tasks will be considered as the criterion to discontinue the study.

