#### Primary outcome

##### Pain intensity

Pain intensity will be measured using the visual analogue scale (VAS). This scale ranges from 0 to 100 mm, with the leftward extreme marked zero (absence of pain) and the rightward extreme marked 100 (worst pain imaginable). VAS scores will be computed by measuring the length of the line in millimetres from the extreme leftward mark (no pain) to the mark made by the participant. For the statistical purposes, the average score of the five valid attempts of each functional task will be used [33].

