##### Acceptable state of symptoms

The acceptable state of symptoms will be assessed by asking the participants the following question: “Considering your usual level of pain and your functional disability to perform daily tasks, if you performed this functional task (level-ground walking or single-leg squat test) with the approach used in this intervention (hip strap or foot orthoses) from now on, would you consider your current state to be satisfactory?” [43]. The participants will answer “yes” or “no”. The question will be posed for both conditions (hip strap and foot orthoses).

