### Statistical analysis plan

Statistical analysis will be conducted with the aid of SPSS (version 22; SPSS Inc., Chicago, IL, USA). The normality and homoscedasticity of the data will be tested using the Shapiro–Wilk and Mauchly tests, respectively. If not normally distributed, data will be transformed to enable the use of parametric tests. All data will be expressed as mean and standard deviation.

Linear mixed models with two fixed factors will be applied to test associations between interventions (control, hip strap, and foot orthoses) and conditions (level-ground walking and single-leg squat test) as well as interactions between interventions and conditions. Linear mixed models were chosen due to the ability to include fixed and random effects and increase the study power by including individuals with missing data in the analysis. Subject and intercept will be included as random effects. The covariance type will be unstructured and the restricted maximum likelihood (REML) estimation method was chosen. When an interaction is significant, the mean difference (MD), standard error (SE), and *P*-value for the pairwise comparisons based on estimated marginal means will be reported. For all analyses, the significance level will be 0.05. Measures such as the 95% confidence interval (CI) and effect size will also be included. Interim analyses will not be performed. No additional analyses will be performed in the trial.

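### Pain-driven stopping removes pain scores from the primary analysis: the outcome needs five valid attempts, and the mixed model cannot correct for cells lost because their own pain was high

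*Protocol article*

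**What the plan says.** - **Outcome.** Under Pain intensity, the protocol states that "the average score of the five valid attempts of each functional task will be used". The Functional tasks sections add that an invalid trial or repetition is replaced by another. Neither place says what is scored when a participant ends a task with fewer than five valid attempts.
- **Stopping.** Under Procedures, after Fig. 1: "The presence of any pain or disability that may be related to the interventions and/or functional tasks will be considered as the criterion to discontinue". Its closing words name the study, not the task, as what is discontinued.
- **Who enters.** Under Sample, entrants must have "pain severity during aggravating activities of ≥ 3 on an 11-point numerical rating scale", with squatting given as an example of such activities. They must also have the "ability to perform a single-leg squat to at least 60° of knee flexion".
- **Analysis.** The Statistical analysis plan section chooses a REML linear mixed model, in part to "increase the study power by including individuals with missing data in the analysis". It states no assumption about why data would be missing, and closes with "No additional analyses will be performed in the trial".

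**The concern.** In a single-session crossover, data are lost mainly when a participant does not finish a task or does not go on to the next condition. Here the stated reason for stopping is pain related to the task or device, and that pain is the primary outcome. The cells most likely to be lost are therefore those with the highest values.

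A likelihood-based mixed model makes good use of incomplete data when the chance of a missing cell depends only on what was observed for that person. If the cell is missing because its own unrecorded value was high, the model in effect predicts it from the person's other, milder cells, and that condition's mean comes out too low.

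The direction depends on where the stops fall. Stops mainly in control shrink a real device benefit. Stops mainly under a device make that device look better than it is. Walking always precedes the squat, so losses would tend to fall on squat cells. The plan describes pairwise comparisons when the intervention-by-task interaction is significant, so if the device effect is larger in the squat, a shrunken squat contrast also weakens the test that leads to them.

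**Working it through.** **1. The plan's own figures.** The protocol gives no stop rate. The nearest figure is the 10% allowance for dropouts: 26/0.90 = 28.9, rounded up to 29 (26 × 1.10 = 28.6 also gives 29). This reproduces and is not in dispute. It protects the number of participants, not the validity of the contrast.

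**2. Exposure.** Three conditions × five valid squats = 15 valid squats per participant, plus 3 × 5 = 15 valid walks.

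**3. The provisions side by side.** (a) A cell's score is the mean of five valid attempts. (b) Pain from tasks or devices is the criterion to discontinue. (c) Incomplete participants enter a REML model on the available cells. (d) No further analysis is made. From (a) and (b), a stopped cell has no score as defined. If the stop ends the study, all later conditions in that person's random order are also missing. From (b) and (c), missingness depends on the value not recorded. From (d), nothing would reveal this.

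**4. Size in millimetres.** None of these inputs is in the protocol; all are assumptions. Squat pain is 55 mm in control and 45 mm with a device, walking pain 30 and 25 mm, between-person SD 16 and residual SD 10. A cell is lost when its value exceeds 70, 75 or 80 mm.

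- Total SD = √(16² + 10²) = √356 = 18.9 mm; within-person correlation = 256/356 = 0.72.
- Control cells lost = P(Z > (threshold − 55)/18.9): 21%, 14% and 9%.
- Device cells lost = P(Z > (threshold − 45)/18.9): 9%, 6% and 3%.
- A random-intercept likelihood model on the remaining cells estimated the true 10 mm squat contrast as 8.7, 9.0 and 9.2 mm. When a stop ended the whole session, it gave 8.7, 9.1 and 9.3 mm.

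A separate attempt-level simulation, with about 10–24% stopping in control and 4–11% per device, gave about 8.5–9.3 mm when stopped cells were dropped: a shortfall of 10 − 9.3 = 0.7 to 10 − 8.5 = 1.5 mm.

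**5. Size in SD units, both directions.** Assumed: total SD 1, within-person correlation 0.5 or 0.8, stops in 5%, 10% or 20% of the squat cells in the condition named.

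| Scenario (true strap − control squat difference) | Correlation | Estimate at 5% / 10% / 20% |
|---|---|---|
| Stops mainly in control, −1.25 | 0.5 | −1.19 / −1.13 / −1.06 |
| Stops mainly in control, −1.25 | 0.8 | −1.24 / −1.21 / −1.15 |
| Stops mainly in control, −0.50 | 0.5 | −0.46 / −0.42 / −0.37 |
| Stops mainly in control, −0.50 | 0.8 | −0.47 / −0.46 / −0.45 |
| Stops only under the device, 0 | 0.5 | −0.05 / −0.11 / −0.20 |
| Stops only under the device, 0 | 0.8 | −0.03 / −0.05 / −0.07 |

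Attenuation runs from about 1% to 26%. The false benefit is 0.03 to 0.20 SD; at the 18.9 mm SD of step 4 that is about 0.6 to 3.8 mm. A higher within-person correlation reduces the bias but does not remove it.

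**6. Does scoring the attempts made help?** In the attempt-level simulation, averaging the attempts made, including the last, gave about 9.8–10.2 mm, even when pain rose over attempts or a stop ended the session. The reason is that a retained score makes later losses depend largely on something observed, which the model can handle.

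**The case against.** **This is detail for a fuller document.** A journal article need not state a missing-data assumption or a rule for partial cells, and a cell with two to four scores is nowhere said to be set to missing. That is correct as far as it goes: loss of the cell is the literal reading, not a stated rule. But the article does more than stay silent. It fixes the five-attempt mean, ties discontinuation to the outcome, offers only the available-data model and closes off further analyses. The closing sentence may be aimed at subgroup or exploratory work, since it follows the one on interim analyses, but as written it excludes a sensitivity analysis too.

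**Stops may be rare.** Entrants must manage the squat, physical inability to undergo the procedures is an exclusion, both tasks and devices are practised beforehand, and there is a 1-min interval between trials. This stands, and it limits the likely size.

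**The bias is small against the noise.** With a residual SD of 10 mm and 29 participants, the SE of a paired contrast is 10 × √(2/29) = 2.6 mm, so 0.7–1.5 mm is about 0.3–0.6 SE. A hard threshold on the cell's own value is also close to a worst case. Both points are fair, but the bias is systematic and its direction is not known in advance.

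**Stronger readings that do not hold.** A reader might infer that the model treats missing cells as wholly uninformative. It does not: it allows missingness to depend on the participant's observed cells, and fails only for dependence on the unobserved pain. A reader might also infer that the acceptable-state outcome is lost for anyone who stops, so that only completers are counted. The Acceptable state of symptoms section does not support this. Its question is hypothetical ("from now on, would you consider your current state to be satisfactory"), is posed for both devices and does not require a completed task, so it can be asked after a stopped device task. There is no ground for scoring such participants as a no in place of their own answer.

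**Conclusion.** The concern holds for the primary pain outcome. Followed literally, the outcome definition, the discontinuation criterion and the missing-data approach together lose cells because of the value being measured, and the plan has no analysis that would show it.

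The size cannot be determined from the protocol. Under assumed stopping of about 10–24% in control and 4–11% per device, a 10 mm squat contrast is understated by roughly 0.7–1.5 mm. Stops mainly under a device would bias the result in that device's favour. Means, SDs, correlations, thresholds and stop rates are all assumptions, and if stops are rare the effect is negligible. This is a change worth making before recruitment, which the Trial status section says has not started. It is not a flaw that invalidates the design.

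**What to change.** - **Pain intensity:** state that when a task ends early, the score is the mean VAS of all attempts made in that task and condition, including the one at which it ended.
- **Statistical analysis plan:** report the number of early ends by condition and task. Amend the closing sentence to allow one sensitivity analysis for cells lost because of pain, including conditions not reached.
- **Procedures, Pain intensity and Statistical analysis plan:** reconcile them on whether a stop ends the task or the study, so that it is clear which cells can be missing. This concerns scoring and analysis only; the clinical stopping criterion is not altered here.

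The cost is a few sentences and one extra model run, with no added participants or visits. The downside is small: a cell based on fewer than five attempts is noisier than a full one.

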## Methods/design

### Aims

The primary aim of the proposed study is to determine the immediate effects of the hip strap and foot orthoses during level-ground walking and the single-leg squat test on self-reported outcomes. The secondary aim is to investigate whether both the hip strap and foot orthoses result in the kinematic changes that they are purported to cause.

The hypothesis is that the hip strap and foot orthoses will result in immediate improvements in pain intensity and other self-reported measures. We also hypothesise that the interventions will result in a decrease in peak femoral adduction and internal rotation as well as a decrease in peak rearfoot eversion.

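### The only rule for device-versus-control contrasts is triggered by a significant intervention-by-task interaction, which is not the question the primary aim asks

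*Protocol article*

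**What the plan says.** The Aims section of the protocol article states the primary aim as "to determine the immediate effects of the hip strap and foot orthoses during level-ground walking and the single-leg squat test on self-reported outcomes". The hypothesis there is that both devices improve pain and the other self-reported measures. It does not say that the benefit differs between the two tasks.

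The Statistical analysis plan section then sets out:

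- **Model.** "Linear mixed models with two fixed factors will be applied to test associations between interventions (control, hip strap, and foot orthoses) and conditions" (walking and squat), "as well as interactions between interventions and conditions".
- **Pairwise comparisons.** The rule opens with "When an interaction is significant, the mean difference (MD), standard error (SE". The rest of that sentence adds the P-value and takes the comparisons from estimated marginal means.
- **Other reporting.** "All data will be expressed as mean and standard deviation"; "Measures such as the 95% confidence interval (CI) and effect size will also be included". The second sentence does not name the contrast to which the interval or effect size belongs.
- **Closing clause.** "No additional analyses will be performed in the trial".

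No sentence says what is reported about each device against control when the interaction is not significant.

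**The concern.** The interaction test and the primary aim address different quantities. The aim concerns the size of each device's effect against control. The interaction concerns whether that effect changes from walking to squatting. The authors' own hypothesis, that both devices reduce pain, is fully compatible with no interaction at all.

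Followed as written, the plan may therefore hold no prespecified estimate of either device's effect on the primary outcome when the devices work and work consistently. What would remain is an omnibus test across three levels and a table of condition means and SDs. A significant omnibus result could come from either device, or from a difference between the two devices. In a within-person design, means and SDs by condition do not give the precision of the difference, because that depends on the within-person correlation. Any contrast added afterwards would be a choice made with the data in view.

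**Working it through.** **Inputs from the protocol article.** Three interventions and two tasks; significance level 0.05 (Statistical analysis plan); minimum sample 26, planned sample 29 (Sample). Within-person correlation and pain SD are not given. They are assumptions below, and effects are in SD units.

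**The article's own figure.** The article gives no figure for this rule. Its sample size can be reproduced. A two-sample t-test with effect size 1.25, two-sided alpha 0.05 and 80% power needs 22.19 observations. With six clusters and an assumed intraclass correlation (ICC) of 0.05:

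- cluster size m = 22.19 × 0.95 / (6 − 22.19 × 0.05) = 4.31
- 22.19 × (1 + 3.31 × 0.05) = 25.86, i.e. 26
- 26 × 1.1 = 28.6, i.e. 29

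The total depends on the assumed ICC: 0 gives 22 and 0.10 gives 32. Nothing below depends on this derivation; 29 is used only as the planned sample.

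**Step 1: what the trigger tests.** For each device let δW and δS be its effect against control in walking and squat. The interaction test has 2 numerator degrees of freedom, one difference δS − δW per device. The task-averaged device effect is (δW + δS)/2. If δW = δS for each device, both interaction differences are zero, whatever the value of δ. The probability that the trigger is met is then the test's size, 0.05. Simulation of a balanced random-intercept model at N = 29 (20,000 runs per setting, effects from 0 to 1.25 SD, correlation 0.3 to 0.7) gave 4.8% to 5.3%.

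**Step 2: what is lost.** In that model the SE of a task-averaged device-versus-control difference is √((1 − ρ)/N), and the t-test has 5 × 28 = 140 degrees of freedom (critical value 1.977). For an equal benefit of 0.5 SD with both devices:

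| Assumed ρ | SE | 0.5/SE | Contrast significant | Contrast significant, trigger not met |
|---|---|---|---|---|
| 0.3 | √(0.7/29) = 0.155 | 3.22 | 89% | 85% |
| 0.5 | √(0.5/29) = 0.131 | 3.81 | 97% | 92% |
| 0.7 | √(0.3/29) = 0.102 | 4.92 | 99.8% | 95% |

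The last column is close to the fourth times 0.95. At 1.25 SD, the effect size in the sample-size statement, the contrast is significant in essentially every trial and the trigger is not met in about 95% of them.

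**Step 3: unequal effects.** Let each device's walking effect be half its squat effect d. The interaction noncentrality is λ = N × ½ × Σ(D − D̄)²/(1 − ρ), with D = (0, −d/2, −d/2). For d = 0.8, Σ(D − D̄)² = 0.1067, so λ = 29 × 0.0533/(1 − ρ) = 1.547/(1 − ρ). This is 2.21, 3.09 and 5.16 for ρ = 0.3, 0.5 and 0.7. The trigger is then met in 24%, 32% and 51% of trials. For d = 1.25 it is met in 53%, 68% and 89%. So the rate runs from low to high according to inputs the article does not supply.

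**The case against.** - **The text says when, not only when.** This is correct. One can read the sentence as covering the within-task comparisons that follow an interaction, with follow-up of a main effect left unstated. The restriction is an inference from the absence of any other rule together with the closing clause. That clause follows a sentence on interim analyses and may be aimed at subgroup or sensitivity work. Even on that reading it supplies no rule for the missing contrasts.
- **A reader might infer that the plan does not report device effects at all.** The article does not support that. The three-level intervention test and the condition means with SDs are reported regardless. The sentence on confidence intervals is not expressly tied to the interaction. What is not assured is a device-versus-control difference with its precision.
- **A reader might also infer that contrasts released by the trigger are exaggerated.** This does not hold in general. With an equal 8 mm effect in both tasks, simulated trials that passed the trigger gave mean strap effects in the squat of −8.2 and −7.8 mm, with no systematic inflation. Some inflation appears under unequal effects (about −12 to −13 mm against a true −10 mm), but that rests on assumed inputs.
- **Equal effects are not the obvious default.** The Procedures section says the squat loads the patellofemoral joint more. This stands, and it is why the unequal-effect rates cannot be given as a single figure.
- **An article condenses.** True of omitted detail. Here, however, a specific reporting rule is stated, and it is conditioned on a test other than the one the aim requires.

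**Conclusion.** The point holds in this form: the only stated provision for pairwise differences is conditional on a test of effect heterogeneity, while the primary aim and hypothesis concern the device effects themselves.

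If each device helps equally in both tasks, the trigger is met in about 5% of trials. That figure needs no assumption about effect size, SD or correlation. It does assume that the interaction test holds its nominal level. With larger pain SDs in the squat than in walking, a random-intercept-only F-test met the trigger in about 1% of simulated equal-effect trials, which would be worse for the plan. The figures of 85% to 95% for a detectable contrast left outside the rule rest on an assumed 0.5 SD benefit and correlations of 0.3 to 0.7. The unequal-effect rates are illustrations only.

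The design, data collection and sample size are not in question.

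**What to change.** Replace the conditional sentence with an unconditional one. For VAS pain, report strap-versus-control and orthoses-versus-control mean differences with SE, 95% CI and P-value from the planned mixed model, whatever the interaction result. Give them averaged over the two tasks and within each task. The averaged contrast answers the equal-benefit case most directly; the within-task contrasts match the two tasks named in the aim.

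State in advance which of these contrasts are primary and how multiplicity across them is handled. Making all four within-task contrasts primary at an unadjusted 0.05 would give up to 1 − 0.95⁴ = 18.5% familywise error if they were independent, and less when they are correlated. Keep the interaction test as supporting information on whether effects differ by task.

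The cost is a sentence or two of analysis wording, a few more prespecified contrasts, and slightly wider intervals if multiplicity is adjusted. No new data and no change in sample size are needed. The Trial status section says recruitment had not started, so on that timetable the change could be made before any data exist.
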